## Abstract

**Background:**

The promotion of health and the interventions in community health continue to be one of the pending subjects of our health system. The most prevalent health problems (cardiovascular diseases, cancer, diabetes...) are for the most part related to life habits. We propose a holistic and integral approach as the best option for tackling behavior and its determinants. The research team has elaborated the necessary educational material to realize group teaching, which we call "Health Workshops". The goal of the present study is to evaluate the effectiveness of these Health Workshops in the following terms: Health Related Quality of Life (HRQOL), incorporate and maintain a balanced diet, do physical activity regularly, maintain risk factors such as tension, weight, cholesterol within normal limits and diminish cardiovascular risk.

**Methods/Design:**

Controlled and random clinical testing, comparing a group of persons who have participated in the Health Workshops with a control group of similar characteristics who have not participated in the Health Workshops.

Field of study: the research is being done in Health Centers of the city of Barcelona, Spain.

Population studied: The group is composed of 108 persons that are actually doing the Health Workshops, and 108 that are not and form the control group. They are assigned at random to one group or the other.

Data Analysis: With Student's t-distribution test to compare the differences between numerical variables or their non parametric equivalent if the variable does not comply with the criteria of normality. (Kolmogorov-Smirnof test). Chi-square test to compare the differences between categorical variables and the Logistic Regression Model to analyze different meaningful variables by dichotomous analysis related to the intervention.

**Discussion:**

The Health Workshop proposed in the present study constitutes an innovative approach in health promotion, placing the emphasis on the person's self responsibility for his/her own health.

The rhythm of a weekly session during 8 weeks with recommended activities to put into practice, as well as the support of the group is an opportunity to incorporate healthy habits and make a commitment to self-care. The sheets handed out are a Health Manual that can always be consulted after the workshop ends.

**Trial registration:**

Clinical Trials.gov Identifier: NCT01440738

## Background

The promotion of health and the interventions in community health continue to be one of the pending subjects of our health system [1,2]. The most common health problems (heart disease, cancer, diabetes...) are related in a large amount to behavior [3-5]. The estimates are that 35% of cancers are diet related [6-8]. The increase of physical activity produces a reduction in the risk of chronic illnesses, like cardiovascular ones, arterial hypertension, type 2 diabetes mellitus and obesity, all of them associated to a sedentary life style [9]. Also, regular physical exercise helps improve mild depressions and anxieties. Some studies have objected that interventions to improve behavior or habits by changing them to healthier ones have resulted in short lived improvements[10-12]. In a systematic revision [13] in diabetes mellitus patients, they have found evidence that group education has had a positive effect for a better metabolic control, the decrease of arterial pressure and overweight, the increase of self control, the quality of life, the development of self care abilities as well as satisfaction with the treatment received, and permits verification of the effectiveness of groups in the incorporation of healthy habits, but that these positive changes do not continue after a time, once the group activity has finished. To continue with this revision and on reflection of the possible reasons of why these positive changes do not continue after a time we find that these studies about health promotion usually deal with specific aspects (physical activity, diet...) [14,15] but do not include other aspects that have influence in behavior and health and well-being.

The biomedical system has a relevant role when approaching ailments in our western society. In spite of the fact that the research team also forms part of the same biomedical system which tends to fraction and specialize, our proposal is centered on a holistic and integrating approach as the best way to tackle health behaviors and its determinants. The proposal is based on Virginia Henderson's model of the concept of nursing [16]; this model has resulted useful in individual caring, and our hypothesis is that this holistic focusing is equally useful to guide other actions of health promotion, as it contemplates the person as a whole giving importance to physical aspects as well as psychical, emotional, cultural and spiritual ones.

Henderson defines the person as whole that has 14 basic activities or requisites to be satisfied in order to maintain a person's health and well being, and develop all his/her capacities. These 14 components are:

Breathe normally, Eat and Drink Adequately, Eliminate Body Waste, Maintain Desirable Positions, Sleep and Rest, Wear Suitable Clothes, Maintain Body Temperature by adjusting clothes and modifying environment, Keep the Body clean and well-groomed, Avoid Dangers and Injuring Others, Communicate with others, express emotions, needs and fears, Worship according to one's faith, Work to have a sense of Accomplishment, Play and Participate in various forms of Recreation, Learn, discover and Satisfy Curiosity. According to this model, everybody is capable of carrying out these basic activities by themselves, and if they don't, it is because of lack of the knowledge, will, or strength to do so.

In the year 2008 the research team developed the necessary educational material to carry out group education which we named "HEALTH WORKSHOPS" [17] addressed to the general public. The workshops consist of 8 sessions with weekly cadence and gather those 14 components described by Henderson. In the different sessions we incorporate tools in order to help integrate healthy habits to daily life and improve the quality of living perceived and have a direct relation to their prevalent health problems. Also these healthy habits are contained in health system plans of all the Autonomous Communities in Spain, and are recommended in the Program of Health Prevention and Health Promotion Activities. (PAPPS) [18]

In spite of not being standard, the measurements of Heath Related Quality of Life (HRQOL), have proved valid and reliable in evaluating health results [19]. Clinical personnel and managers have recognized the importance of measuring the HRQOL as useful in informing about the most effective patient handling and in decision making in matters of health [20]. These measurements include health profiles in which the general questionnaire of Medical Outcomes Study 36 item Short Form Health Survey (SF-36) stands out, containing 36 items that cover two areas, the functional state (4 physical dimensions) and the emotional well-being (4 mental dimensions) [19]. Furthermore this questionnaire has normative population values for the Spanish population [21,22] for which reason we consider using it as the main variable in the study.

## Hyphotesis

The Group Intervention of Health Promotion that this study proposes (which contemplates in an integral way biological, physiological, social, cultural and spiritual aspects of the person related to health and well-being), improves the quality of life related to health (HRQOL) and facilitates the incorporation and keeping of healthy habits.

### Objectives

#### Principal objective

Assess the effectiveness of the Health Workshops, in terms of HRQOL measured by the SF-36 Questionnaire.

Secondary objectives:

1.) To know the effectiveness of the Health Workshops in relation to:

• Incorporating and maintaining a balanced diet.

• Keeping up a regular physical activity.

• Maintaining risk factors (Blood Pressure, Weight, and Cholesterol) within normal limits.

• Risk reduction cardiovascular disease (CVD)

2.) To make an estimate of the costs of the Health Workshop.

## Method/Design

Design: Cluster randomized trial, controlled and multicentric, comparing one group of patients that take part in the Health Workshops, with another group of similar characteristics that don't.

Setting: The study will be done in Heath Care Centers of Barcelona City.

Randomization unit: Primary care Teams (PCT)

Study Population: Population around the Centers that participate in the Study and that meet the criteria of inclusion.

Inclusion criteria:

• Persons of both sexes between 18 and 65 who consent to do so.

Exclusion criteria:

• If there is an objection to participating during a period of 12 months.

• If there a language difficulty, unable to understand or express in Spanish or Catalan.

• If there are acute mental problems.

• Other health problems which may be a difficulty in following the workshop, (like terminals, organic pathology...).

Sample size calculation: Accepting an Alfa risk of 0.05 and a Beta risk of 0.2 in a bilateral contrast, 108 individuals per group are needed in order to detect how statistically effective it is in a 20% difference between groups in quality of life with the SF-36 Questionnaire. We have estimated a 10% rate of loss in participation. The ARCOSENO approximation has been used.

Variables in the study: We collect socio-demographic variables from all participants: age, sex, studies, employment or work situation.

Principal Variable: HRQOL measured by means of SF-36 Questionnaire. We have selected the quality of life perceived indicator as the main variable as it is sensible to small changes [19].

Variables related to the intervention:

• Number of sessions the person has attended.

• IPAC Questionnaire for variables related to physical activity (the IPAC questionnaire has been used in research around this area so it allows us to compare the data obtained.)

• The variables related to eating habits will be collected by means of Questionnaire PREDIMED [15], which is validated and used in our area, as so allow us to compare results.

• Blood Pressure, Lipid Profile, Height, Weight, will be gathered from the computerized clinical history.

• To estimate the costs we will add the time spent by professionals directly related with the intervention (telephone calls, meetings with participants, gathering of data, workshops...)

• Gathering of information: the gathering of data will be done in both groups, (intervention and control groups): before each intervention (Health Workshop), at the end of the intervention and in 6 months and 12 through self administered questionnaires in Teleform^© ^format.

Description of the Study (Figure 1)

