**Figure 1 F1:**
[figure not shown]
**Algorithm of the study**.

The stages of this study are the following:

Phase Recruitment and selection:

1 The recruitment of the PCT: The project is explained to professionals belonging to the Health Centre. Those interested in participating in the recruiting of patients will sign a commitment of participation in the Project. The participants will be recruited by these professionals and their inclusion will be consecutive. Once the recruitment has ended, the groups will be randomized in the intervention or control group. Persons interested will fill up an application form for the Workshop, which will be available in their Health Care Center (HCC) and where they have to give their name, phone number, and time availability.

The Blood Pressure (BP) and Weight data will be gathered (in those persons who consent), at an individual visit after the informative meeting. They will be asked to have a Lipid Profile (if it is not available in their clinical history in a 3 months period before the workshops begins), and again after 12 months.

Phase The Forming of the Study Groups

2 Based on the persons who have given their consent to participate, an random assignation to one or another group will take place, and the workshops will then start (with groups of 12 to 15 persons in each).

Phase Intervention (only in the group intervened)

3 The group intervention then starts in 8 sessions in which life activities will be approached in a progressive manner. During the sessions, tools will be offered to increase knowledge and develop abilities and motivations that help with life activities and the progressive incorporation of healthy habits. At the end of each session support material will be handed out with the session's contents and indications of activities to practice during the week.

The workshops will be offered at different schedules to facilitate assistance. The contents of the sessions are in Table 1.

**Table 1 T1:** Subject matter of the sessions in the work shop

Session	Content
1	Breathing. Tobacco, learning from experience.

2.	Eating and drinking adequately, a balanced diet.

3.	Elimination. The importance of regular disposal. Guides to avoid constipation. Hygiene. The importance of personal hygiene.

4.	Movement and maintaining adequate positions. Doing physical activity. Wearing adequate clothes.

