### Data analysis

The analysis will be done on an intention to treat basis. Those who have done less than six sessions will be considered withdrawals.

The descriptive analysis will be done in proportion to the quality variables and the average values for the quantities, with the corresponding measures of dispersion.

To observe the effect of the intervention in quality of life related to health, the change of habits and the costs derived from related resources, the T-Tests will be used for paired data and the McNemar Test or equivalents for quantitative or qualitative variables or their non parametric equivalents, if the distribution of the variable does not comply with the criteria of normality (Kolmogorov-Smirnof).

To analyze the factors that have influence over the changes of quality of life related to health (CVRS) and those related with the intervention, models of multiple regressions will be used. In each regression model the dependent variable will be derived from the calculation or the difference between ratings in the beginning of the study and the ratings at the end of the SF-36; the rest of the variables determined in the study will be included as independent variables. As the first step in the analysis of regression the adequate diagnosis will be done to detect extreme values and verify conditions of applicability (homocedastisity, normality and independence of waste). If needed the necessary transformations will be done in the dependent variables for the fulfillment of applicability conditions. The criteria of selection of variables for the estimation of multivariable models will be a Forward-Stepwise with the criteria of input of p < 0.05 and a criteria of output of p > 0.10.

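### Primary care teams are declared the randomisation unit, but every between-arm test and model named assumes independent persons; the unit itself must also be reconciled

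*Protocol article*

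**What the plan says.** Method/Design is explicit about the design, "Design: Cluster randomized trial, controlled and multicentric", and about the unit, "Randomization unit: Primary care Teams (PCT").

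The analysis methods are named in two places. The Abstract gives Student's t-test or a non-parametric equivalent for numerical variables, and "Chi-square test to compare the differences between categorical variables and the Logistic Regression Model" for the rest. The Data analysis section gives paired t-tests, McNemar or equivalents, and multiple regression on the change in SF-36 with forward-stepwise selection. It says the regression diagnostics will "verify conditions of applicability (homocedastisity, normality and independence of waste"). If they fail, the stated response is to transform the dependent variable. No method carries a team term, a random effect, a robust variance or a team-level summary, and team is not among the variables listed in Method/Design.

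Two other places read as allocation of persons. The Abstract says of the participants: "They are assigned at random to one group or the other". The phase on forming the study groups says: "Based on the persons who have given their consent to participate, an random assignation to one or another group will take place". The same sentence adds that workshops run "with groups of 12 to 15 persons in each".

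**The concern.** When whole teams are allocated, persons from one team share staff, neighbourhood and recruitment, so their outcomes may be correlated. Methods that count each person as an independent observation then credit the trial with more information than it holds. Standard errors are too small by the square root of the design effect, confidence intervals are too narrow, and the workshops can be declared effective too often.

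This is more than detail left to a later document. The article fixes its tests, its regression model, its selection thresholds and its diagnostics, and these conflict with its own declared design. It even lists independence of residuals as a condition to be checked, but the repair it offers leaves persons in the same team correlated on the new scale. Stepwise selection by p-value would also work from the understated standard errors.

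The consequence is practical: SF-36 quality of life is the principal objective, and the offer of workshops to the control group depends on effectiveness having been shown.

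**Working it through.** **1. The plan's own sample size.** Inputs from Method/Design: "Accepting an Alfa risk of 0.05 and a Beta risk of 0.2 in a bilateral contrast", a 20% difference, the arcsine approximation, 10% loss, 108 per group. The baseline proportion is not given; 40% versus 60% is assumed here.

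- h = 2·asin(√0.6) − 2·asin(√0.4) = 0.4027
- n = 2·((1.960 + 0.842)/0.4027)² = 96.8, rounded up to 97
- 97/(1 − 0.10) = 107.8, rounded up to 108

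Under that assumption the figure reproduces exactly with a design effect of 1. Other baselines do not match: 50% versus 70% gives 104, and 60% versus 80% gives 90. So 108 is consistent with a calculation for individually randomised persons.

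**2. If teams are randomised.** Not stated, hence assumed: persons per team m (12 to 36, which is 9 to 3 teams per arm at 108 per arm) and ICC (0.01 and 0.05).

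- Design effect: DE = 1 + (m − 1)·ICC
- Actual two-sided error of an unadjusted 5% test: 2·(1 − Φ(1.96/√DE))

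| m | DE, ICC 0.01 | Error | DE, ICC 0.05 | Error |
|---|---|---|---|---|
| 12 | 1.11 | 6.3% | 1.55 | 11.5% |
| 15 | 1.14 | 6.6% | 1.70 | 13.3% |
| 27 | 1.26 | 8.1% | 2.30 | 19.6% |
| 36 | 1.35 | 9.2% | 2.75 | 23.7% |

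Simulated two-sample t-tests on clustered normal data (20,000 replicates each) agree. At ICC 0.01 and 0.05 they give 6.3% and 12.1% for 8 teams of 13 per arm, 8.1% and 20.4% for 4 of 27, and 9.4% and 23.5% for 3 of 36. At ICC 0 they give 4.6% to 5.1%.

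**3. If persons are randomised.** Shared team effects largely cancel between arms. What remains is grouping by workshop, in the intervention arm only. With equal arms the variance of the difference is inflated by about (DE + 1)/2.

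- ICC 0.01: m = 12 gives (1.11 + 1)/2 = 1.055, error 5.6%; m = 15 gives (1.14 + 1)/2 = 1.07, error 5.8%
- ICC 0.05: m = 12 gives (1.55 + 1)/2 = 1.275, error 8.3%; m = 15 gives (1.70 + 1)/2 = 1.35, error 9.2%

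**4. Power once clustering is respected (teams randomised, 40% versus 60%).** Power = Φ(h·√(97/(2·DE)) − 1.96).

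- m = 12: 75.9% at ICC 0.01 and 61.5% at ICC 0.05
- m = 36: 67.5% and 39.4%

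Keeping 80% would need 108·DE per arm: 120 to 168 for m = 12, and 146 to 297 for m = 36. Few teams would lower power further, because the reference distribution then has few degrees of freedom.

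**The case against.** The strongest objection is that the document does not settle the unit. The Abstract and the phase on forming the study groups both read as allocation of persons. If both arms sit within each team, ignoring team does not inflate the error as in step 2, and a t-test on team means would not fit the design. This stands: the unit must be stated before a method is chosen, and the larger figures are conditional on teams. It does not clear the plan, because the workshops, where group support is meant to be part of the benefit, would still cluster the intervention arm.

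A reader might take the workshop size of 12 to 15 as the cluster size in both arms. The document does not support that: workshops run only in the intervention arm, and persons per team are not given. A reader might also use an ICC of 0.10 and arrive at errors of 18% to 30%. Nothing in the document supports that value. Because the regression outcome is the change in SF-36, the relevant ICC is that of change, from which stable differences between teams have been removed.

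The paired t-test and McNemar test compare a person before and after, so the error rates above do not describe them. That they do not compare the arms is a separate matter.

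Finally, a condensed article may leave estimation detail to the full protocol. That helps little here, because the methods are explicitly named and conflict with the stated design.

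**Conclusion.** The point holds in conditional form. As written, the article declares randomisation of primary care teams and fixes between-arm methods that assume independent persons, with a fallback that cannot deal with clustering. Under team randomisation the direction of the error is certain for any positive ICC; at ICC 0 there is no inflation. The size cannot be read from the document.

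- Teams randomised, 12 to 36 persons per team: about 6-9% at ICC 0.01 and 12-24% at ICC 0.05, against a nominal 5%.
- Persons randomised, workshops of 12 to 15 in one arm only: about 5.6-5.8% and 8-9%.

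Confidence is high in the mismatch between design and analysis, and lower in any single number. The mismatch should be corrected before the data are analysed.

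**What to change.** 1. Reconcile Method/Design (teams) with the Abstract and the phase on forming the study groups (persons). State one unit of randomisation, the number of teams and the expected persons per team.
2. If teams are the unit: estimate the between-arm effect with a mixed model that has a random intercept for team and small-sample degrees of freedom such as Kenward-Roger. If teams are few, use a t-test on baseline-adjusted team means with (number of teams − 2) degrees of freedom. Report the ICC.
3. If persons are the unit: adjust for centre and use a partially nested model, with a random effect for workshop group in the intervention arm only.
4. Restate the power, with the assumed ICC and design effect shown.

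Cost: the analysis change is wording and modest extra work, and needs each participant's team and workshop group on record. Confidence intervals will be wider. If teams are the unit, 108 per group will give less than the stated 80% power, as step 4 of the working shows. The sponsor must then either accept and report the lower power or revisit the number of teams and participants.

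### Under the declared cluster design, 108 per group is an individual-level figure with no design effect, so Beta 0.2 is unsupported for any appreciable intracluster correlation

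*Protocol article*

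**What the plan says.** The Method/Design section describes the study as "Cluster randomized trial, controlled and multicentric" and gives the unit as "Randomization unit: Primary care Teams (PCT").

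The sample size paragraph of the same section sets the error rates and the resulting number together: "Accepting an Alfa risk of 0.05 and a Beta risk of 0.2 in a bilateral contrast, 108 individuals per group are needed". The target is expressed as "in a 20% difference between groups in quality of life with the SF-36 Questionnaire". A 10% loss is assumed, and the method is named: "The ARCOSENO approximation has been used". No base rate, ICC, design effect, number of PCTs or persons per PCT is among the inputs.

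Two other places describe the allocation differently. The Methods/Design part of the Abstract says that the participants themselves are allocated at random. The phase on forming the study groups bases the random assignment on the persons who have consented, and then starts workshops "with groups of 12 to 15 persons in each". That last figure is the size of a workshop group, not the number of participants from a PCT.

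**The concern.** People recruited by the same primary care team tend to resemble one another. When teams are randomised, this correlation inflates the variance of the comparison between groups by the design effect. A sample size computed for independent individuals then gives less power than stated.

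The paragraph makes a firm power claim for the principal outcome, directly after naming the PCT as the unit. If that claim does not belong to the declared design, a null result on SF-36 could be read as good evidence of no effect from a trial with 80% power, when the power was lower by an unknown amount.

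**Working it through.** **Inputs from the article (Method/Design):** two-sided alpha 0.05, power 80%, 20% difference, 10% loss, arcsine approximation, equal groups of 108.

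**Assumed, because the article gives no figure:** base rates of 40% and 60%; ICC of 0.01, 0.05 or 0.10; 12 to 15 persons per PCT, borrowed from the workshop group size as an illustration.

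**Step 1: reproduce 108.**
- h = 2·asin(√0.6) − 2·asin(√0.4) = 0.4027
- n = 2(1.960 + 0.842)²/h² = 96.8, rounded up to 97
- 97/0.9 = 107.8, rounded up to 108

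The individual-level formula plus the 10% loss uses up the whole 108.

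**Step 2: how far this depends on the base rate.** For other absolute 20-point contrasts, the same formula with 10% loss gives 107 (35% vs 55%), 104 (30% vs 50%), 98 (25% vs 45%) and 90 (20% vs 40%). Among the contrasts tried, only 40% vs 60% returns 108. It is also the contrast that needs the most participants. At 20% vs 40% there would be slack of 108/90 = 1.2, but nothing in the text presents such slack as a design effect.

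**Step 3: what 108 can absorb.** If nobody is lost, the tolerable design effect is 108/96.8 = 1.12. Solving 1 + (m − 1)·ICC = 1.12 gives an ICC of about 0.011 at m = 12 and 0.008 at m = 15.

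**Step 4: illustrative power.** DE = 1 + (m − 1)·ICC and power = Φ(h·√(97/(2·DE)) − 1.96). The detectable difference at 80% power, centred on 50%, is sin(h·√DE/2). The number needed is 97·DE rounded up, divided by 0.9 and rounded up.

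| ICC | DE (m = 12 to 15) | Power | Detectable difference | Needed per group |
|---|---|---|---|---|
| 0 | 1 | 80.1% | 20 points | 108 |
| 0.01 | 1.11 to 1.14 | 75-76% | about 21 points | 120-124 |
| 0.05 | 1.55 to 1.70 | 58-62% | 25-26 points | 168-184 |
| 0.10 | 2.10 to 2.40 | 44-49% | 29-31 points | 227-259 |

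A t reference on the 7 to 9 PCTs per group implied by 108/15 and 108/12 takes off roughly a further 5 to 7 percentage points. With 4 PCTs per group (m = 27) and ICC 0.05, DE = 2.30 and power is about 46%, or 34% with a t reference.

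**Step 5: the same contrast on a continuous score.** The Data analysis section plans t-tests and regression on the change in SF-36. If 40% vs 60% reflects a shifted normal score, the standardised difference is 2 × 0.2533 = 0.507. About 61 per group are then needed, and 97 analysed would tolerate DE = 97/61 = 1.59. At ICC 0.05 and m = 12 to 15, power would be about 81% to 77%. This assumes normality and the same ICC on the continuous scale, where it may be somewhat higher.

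**The case against.** **The unit is not settled.** The Abstract and the phase on forming the study groups read as assignment of persons. If persons are randomised, the PCT design effect does not apply in this form. This stands, and it makes the point conditional on the design declared in Method/Design. It does not clear the calculation, because delivery in workshop groups could still induce correlation in the intervention arm, which the calculation also ignores.

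**A reader might infer that Beta 0.2 holds only at an ICC of exactly zero.** That is true only at 40% vs 60% with the full 10% loss. With all 108 analysed, ICC 0.01 and m = 12, power is still 80.2%.

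**A reader might take 44-76% as the trial's actual power.** The article gives neither an ICC nor a PCT size. The 12 to 15 belongs to workshops: a PCT could run several, and control PCTs run none during the study. The figures also apply to a dichotomised outcome, and on a continuous SF-36 score the shortfall could be much smaller, as step 5 shows.

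**The full protocol may hold the ICC and the number of PCTs.** A condensed article may leave these out, and their absence is not the fault raised here. The fault is that the published 108 is what its own listed inputs give for independent individuals. An ICC recorded elsewhere would not put a design effect into that number.

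**Conclusion.** The point holds for the design declared in Method/Design. The 108 per group is reproduced exactly as an individual-level sample size plus 10% loss, and clustering does not enter it. This rests on one inferred input, the 40% vs 60% base rate, which is the likeliest reading but is not documented.

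The stated Beta of 0.2 is therefore unsupported for any appreciable ICC: at best, with no losses, the figure tolerates a design effect of about 1.12. The direction of the error is clear if PCTs are randomised. Its size is not, and the power range in the table is illustrative. Fewer and larger PCTs or a t reference would lower power further; a continuous analysis of SF-36 would reduce the shortfall.

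The article does not support the unconditional statement that this trial lacks 80% power, because its own descriptions of the randomised unit conflict and the quantities that fix the loss are not given.

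**What to change.** 1. Reconcile the Abstract, the Method/Design section and the phase on forming the study groups, so that all three name the same randomised unit.
2. If PCTs are randomised, keep the 216 participants and rewrite the sample size paragraph. Give the base rates used, the number of PCTs and persons per PCT, an assumed ICC with a range, the design effect 1 + (m − 1)·ICC, and the resulting power or detectable difference for the outcome as it will be analysed. Withdraw the unqualified Beta of 0.2.
3. If persons are randomised, correct the declared design and restate power allowing for clustering by workshop group in the intervention arm.

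The cost is a rewritten paragraph and consistent wording elsewhere, with no extra participants. The stated power becomes less favourable, and the change discloses the shortfall without removing it. Spreading recruitment over more PCTs with fewer persons in each would help statistically, but it is not a wording change and sits awkwardly with workshops of 12 to 15, so it is not part of this fix.

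### The 108 per group comes from a two-proportion (arcsine) calculation, but the SF-36 is analysed as a difference in ratings, so the stated 80% power does not describe the principal variable as analysed

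*Protocol article*

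**What the plan says.** The sample size statement is in Method/Design of the protocol article. Its error rates are set by "Accepting an Alfa risk of 0.05 and a Beta risk of 0.2 in a bilateral contrast", and it concludes that "108 individuals per group are needed". The target is a "20% difference between groups in quality of life with the SF-36 Questionnaire". Attrition is covered by "We have estimated a 10% rate of loss in participation", and the method is named last: "The ARCOSENO approximation has been used". No pair of proportions, mean difference or SD accompanies these figures.

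The Background describes the SF-36 as covering two areas, "the functional state (4 physical dimensions) and the emotional well-being (4 mental dimensions"). Method/Design makes the questionnaire the principal variable, without naming a particular score.

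The Data analysis section sets the dependent variable of the regression models as "the difference between ratings in the beginning of the study and the ratings at the end of the SF-36", with checks of normality and constant variance. It also lists paired t-tests and McNemar tests for quantitative and qualitative variables. The Abstract lists Student's t for numerical variables, and chi-square and logistic regression for categorical or dichotomous ones.

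**The concern.** A power statement is useful only if the effect it names is on the scale of the planned comparison. The arcsine method takes two event rates and returns a number of people. It uses no mean and no SD. A change in SF-36 rating is a numerical variable, and its detectable difference depends on the SD of the score.

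The 20% therefore has no fixed meaning for the outcome as analysed. It could be 20 percentage points in the share of people who improve, a 20% relative rise in that share, or 20% of a mean score. These imply very different trials. Since this is the only justification for the trial's size, a reader of the results could not say what difference in SF-36 the trial was able to detect. In particular, a null result could not be interpreted against a planned effect.

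**Working it through.** **Inputs from the article.** Two-sided alpha 0.05 (z = 1.960); power 0.80 (z = 0.8416; sum 2.8016); 10% loss; equal groups of 108 (Abstract and Method/Design); arcsine approximation; a 20% difference. Event rates are not given and have to be inferred.

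**1. Reproducing the 108.** The arcsine formula is n = 2 × (2.8016 / h)², with h = 2·asin√p₂ − 2·asin√p₁.

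- For 40% versus 60%: h = 0.4027, n = 96.8, rounded up to 97.
- With 10% loss: 97 / 0.9 = 107.8, rounded up to 108. This matches the article.

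Other readings of 20%, each including 10% loss:

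| Rates | n per group |
|---|---|
| 35% vs 55% | 107 |
| 30% vs 50% | 104 |
| 20% vs 40% | 90 |
| 50% vs 60% (relative 20%) | 431 |
| 75% vs 90% (relative 20%) | 108 |

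Two of the pairs checked give 108, so the rates cannot be identified with certainty. Both are proportions, and neither calculation contains an SF-36 mean or SD.

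**2. What the same size gives for a difference in means.** Analysable per group: 108 × 0.9 = 97.2, taken as 97. The detectable standardised difference at 80% power with independent observations is 2.8016 × √(2/97) = 0.402 SD.

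In SF-36 points this depends on an SD that the article does not give. For assumed SDs of 10, 20, 25 and 30 it is 4.0, 8.0, 10.1 and 12.1 points.

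**3. Does this show too little power?** Power with 97 per group is Φ(δ / (SD × √(2/97)) − 1.96). All differences and SDs here are assumptions:

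| Difference | SD 10 | SD 20 | SD 25 |
|---|---|---|---|
| 5 points | 94% | 41% | 29% |
| 10 points | >99% | 94% | 80% |

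If 20% meant 20% of a mean score, then with an assumed mean of 70 the target is 0.20 × 70 = 14 points. The number needed before loss would be 33 per group at SD 20 and 51 at SD 25, well under 97. Power may lie on either side of 80%.

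**4. Clustering.** Method/Design names Primary Care Teams as the randomisation unit. The variance of the group difference is then multiplied by the design effect (DE), so the detectable difference is 0.402 × √DE. The article gives no intracluster correlation or number of teams, so DE is unknown. For illustration only:

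- DE 1.5: 0.402 × 1.225 = 0.49 SD. Power at 0.402 SD is Φ(2.80/1.225 − 1.96) = Φ(0.33), about 63%.
- DE 2.0: 0.402 × 1.414 = 0.57 SD. Power at 0.402 SD is Φ(2.80/1.414 − 1.96) = Φ(0.02), about 51%.

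**The case against.** The best defence is that the article keeps methods for binary outcomes in play. The Data analysis sentence on the effect of the intervention, which includes quality of life, lists McNemar's test beside paired t-tests, and the Abstract lists chi-square and logistic regression. The regression on the SF-36 difference is presented as a study of influencing factors and is not called the primary between-group test. A dichotomised SF-36 analysis is therefore not excluded. This stands as far as it goes. However, those methods are assigned to qualitative or dichotomous variables, the article never turns the SF-36 into one, and the only analysis specified for the SF-36 by name uses a difference in ratings.

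A second defence is that this is a condensed article, so missing rates, SDs or cut-offs may be in the full protocol. That is fair, and their absence is not the point. The point is that the article states both a calculation method and an analysis scale, and the two disagree.

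Several stronger readings are tempting but not supported:

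- A reader might infer that the 108 is miscalculated. It is correct on its own terms.
- A reader might infer that the trial is underpowered. The low figures above rest on a 5-point target and on SDs that the article does not state, and other readings give ample power.
- A reader might infer that the trial is sized for a large effect, given that the SF-36 was chosen for its sensitivity to small changes. The article's 20% cannot be converted to an SF-36 effect, so this cannot be established.
- A reader might infer from the eight dimensions that false-positive error is inflated. The article does not say that each dimension will be tested at 5%.
- A reader might infer that the primary visit is wholly open. The wording is loose, but the rating at the end, together with a last evaluation at 12 months, points to the final visit.

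**Conclusion.** The point holds as a mismatch between method and outcome. The 108 per group is a two-proportion sample size, while the principal variable is analysed as a difference in ratings with no responder proportion defined. The 20% difference and its 80% power therefore do not describe the outcome as analysed, and the direction of any error in power is unknown.

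What the planned size does offer for means is about 0.40 SD at 80% power. This assumes 97 analysable people per group, a two-sided 5% test and independent observations. Under the stated randomisation of teams, any design effect above 1 makes the detectable difference larger than 0.40 SD or, equivalently, puts power at 0.40 SD below 80%. The 40% and 60% rates are inferred, and every SD, mean and design effect used above is an assumption. The conclusion does not depend on them. It should be corrected because this is the trial's only power statement.

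**What to change.** Name one SF-36 score at the final 12-month evaluation as the primary variable. Replace the arcsine sentence with the difference in means that the planned size can detect: with 97 analysable per group, about 0.40 SD at 80% power under independence, multiplied by the square root of a stated design effect. The text should not claim 80% power at 0.40 SD and also a design effect above 1 at the same enrolment. Any conversion to SF-36 points should give its assumed SD.

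The alternative is to define an SF-36 responder, state the expected proportion in each group, and make the comparison of those proportions the primary analysis. Calculation and analysis would then agree, although the design effect would apply there too.

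Either route changes only protocol wording and leaves enrolment as it is. The cost is that the published figure becomes less favourable once clustering is allowed for.
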